#### Data sharing

In accordance with the ethics committee approval and the 2015 German Research Foundation (DFG) guidelines for the handling of research data, the quantitative individual patient data will be made publicly available in a de-identified form. The full data package (i.e. analyzable data set, protocol, statistical analysis plan, statistical programming code) will be made freely available through a clinical data repository (e.g. Dryad Digital Repository) and saved for at least 10 years. Data sharing will follow the FAIR Data Principles (Findable, Accessible, Interoperable, and Reusable) and international naming conventions (e.g. Systematized Nomenclature of Medicine) to maximize transparency and scientific reproducibility.

#### Informed consent

Before inclusion, eligible participants are informed about the study procedure and data protection verbally and in written form by the local research team. They are also informed that consent to participate is voluntary and can be withdrawn at any time without giving reasons, and without any disadvantages. Written information will be provided in participants’ local language and checked by a patient representative regarding comprehensibility beforehand. Written informed consent forms will be signed by all participants and sent to the local research team. Participants will receive a financial compensation for their participation in the study.

#### Risks and benefits

In general, psychosocial support interventions bear no major risk for severe adverse events. In our efficacy trial [15], no major adverse events occurred and no individual stated that the intervention harmed them. Rather, participating in the intervention was beneficial for patients. Being involved as a peer-counselor can potentially be beneficial, too [53]. However, adverse events unrelated to the intervention may occur. If suicidal ideation is detected (e.g. during selection interviews or in peer-counseling sessions), we will apply a proven algorithm (e.g. contact the physician or consider psychiatric treatment) that is already available from other studies of the project team. Before the trial, the staff (including peer-counselors) will be carefully advised to follow these guidelines and provided with an emergency number. In cases of acute suicidality, the patient will be transferred to receive psychiatric treatment and excluded from the study. Any questions regarding patient exclusions, serious adverse events, and potential study termination will be reported to and reviewed by the DSMB. The DSMB will annually monitor the study and evaluate the collected study data with regard to participant safety, study conduct, compliance with the study protocol and progress. Where appropriate, recommendations will be made to continue, modify, or terminate the study or to unmask participants in case of adverse events. For the individual patient, the trial procedure will stop if any adverse events or withdrawal of informed consent occur. The whole trial will be discontinued if the consortium or the DSMB detect significant associations between study participation and adverse events. 

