#### Sample size

Our primary effectiveness outcome is the group difference in the baseline-adjusted mean score in mental health-related quality of life at post-assessment, assessed with the Short-Form Health Survey (SF-12 [28]). Taking the results of our prior randomized controlled trial (RCT) into account [15], we assume a between groups effect size of *d* = 0.4. Based on two-sided testing with α = 0.05 and 1-β = 0.8, *N* = 100 patients are needed per group (intention-to-treat analysis), yielding in *N* = 200 to be analyzed. Considering our prior RCT [15], we conservatively expect an inclusion rate of 60% and approximately 15% loss to follow-up. Thus, *N* = 240 patients will be included, for which we expect to invite a total of *N* = 400 patients for participation at the five study sites over 15 months.

For the quantitative implementation part of the trial, all patients in the intervention group (*N* = 100), all peer-counselors (~ *N* = 40) and all involved healthcare providers (~ *N* = 25) will be invited to participate in the survey. With an estimated response rate of 80% [15], we expect to include *N* = 132 participants across all sites. At least *N* = 5 participants per stakeholder group and site will be invited to take part in the focus groups, resulting in an estimated sample size of *N* = 100 in total.

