### Assessments and outcomes

We will assess quantitative outcomes in both groups at three time points: at baseline (t0), directly after patients in the intervention group completed the program (t1), and at a three-month follow up (t2). Sociodemographic and clinical variables will be assessed at baseline using single items. Qualitative data will be assessed after the follow-up assessment is completed (t3).

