#### Effectiveness focus

Each partner will recruit eligible patients on a national level by informing them about the study in their routine care. In case this does not suffice to reach the targeted sample size, each partner receives support by a collaborating national patient advocacy organization (PAO), who will recruit nationwide via their homepage, patient journal, newsletter etc. Inclusion and exclusion criteria will be assessed in a structured interview by trained research personnel. Eligible participants will sign an informed consent form. Participants will then be randomly assigned to either the intervention group or a control group. The intervention group will complete the six-week program from home in addition to CAU, whereas the control group will receive CAU alone. After the last data assessment, patients in the control group can participate in the program outside of the trial.

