#### Methods against bias

A fixed randomization schedule (allocation ratio 1:1) will be conducted electronically to avoid any preferential patient allocation to the two conditions. Randomization will be conducted by a researcher who is not involved in data assessment and intervention delivery. Neither the patients nor the researchers have any influence on the randomization procedure. *Electronic data collection.* Data will be directly entered into electronic databases by the patients. Thus, error-prone transfer from paper to the electronic databases will be avoided. *Standardization of intervention.* Peer-counselors will be trained and supervised and the intervention is described in peer-counseling guidelines. After each session, peer-counselors will complete a short protocol to assess adherence to the program content. *Blinding.* a) Raters: Outcome assessments will be either self-reported or performed by trained raters who are fully blinded regarding group allocation and not involved in intervention delivery. Thus, Q.RARE.LI is fully observer-blinded. b) Peer-counselors and patients: As in most psychotherapeutic intervention studies, full patient and therapist blinding is not feasible as their active involvement in the intervention is necessary. However, peer-counselors will not be informed about the patient’s group allocation. *Minimization of patient drop-out.* At follow-up, patients will be contacted by telephone according to a schedule of repeated contact attempts. *Standardized report of trial and results.* The trial and the results will be reported according to the CONSORT 2010 recommendations (www.consort-statement.org/).

All data on human subjects will be recorded, handled, and stored by the rules of the General Data Protection Regulation (GDPR). A Data Safety and Monitoring Board (DSMB), independent of the project team and consisting of internationally recognized experts in rare diseases and psychosocial treatments, will oversee the conduct of this study. Before the trial starts, we will prepare a data management plan and all partners will sign a data protection agreement in which they commit to comply to the GDPR.

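### The individual stop rule is triggered by any adverse event and does not protect the t1 and t2 assessments, so primary-outcome scores can be lost for reasons related to mental health

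*Protocol article*

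**What the plan says.** The stop rule is in the Risks and benefits section of the protocol article: "For the individual patient, the trial procedure will stop if any adverse events or withdrawal of informed consent occur". The same section anticipates events with no link to treatment: "However, adverse events unrelated to the intervention may occur". It also covers suicidality: "If suicidal ideation is detected (e.g. during selection interviews or in peer-counseling sessions), we will apply a proven algorithm". In acute cases, "the patient will be transferred to receive psychiatric treatment and excluded from the study".

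Other sections assume that outcomes are collected from everyone randomised:

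- Assessments and outcomes: "We will assess quantitative outcomes in both groups at three time points" (baseline, t1 after the program, t2 three months later).
- Sample size gives its requirement on an intention-to-treat basis: "patients are needed per group (intention-to-treat analysis".
- Methods against bias, on limiting drop-out: "At follow-up, patients will be contacted by telephone according to a schedule of repeated contact attempts".
- Effectiveness focus describes the intervention arm as program plus care-as-usual, "whereas the control group will receive CAU alone".

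**The concern.** The rule treats an adverse event like withdrawal of consent. Withdrawal may properly end data collection. An adverse event is a reason to consider stopping the intervention, but not in itself a reason to stop measuring the patient. Since any event counts, even an unrelated one triggers the rule.

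The primary outcome is mental health-related quality of life at t1. An adverse event or acute suicidality between baseline and t1 is plausibly linked to that score beyond what the baseline score predicts. A patient whose assessments end then has neither t1 nor t2. The planned hierarchical model takes the baseline score as a covariate, so such a patient contributes no outcome to it. The imputation described in Data analysis may not recover a score that is missing because of a post-baseline event.

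Detection could also differ between arms. Of the two example places for detecting suicidal ideation, selection interviews come before randomisation. Peer-counseling sessions come after it, and during the trial only the intervention arm has them. If more intervention patients with poor scores were stopped, the estimate would favour the intervention. The list of places is only illustrative, so this difference is possible but not shown.

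**Working it through.** **1. Does the rule reach the assessments?** *Trial procedure* is undefined and could mean the program only. Four features of the text support the wider reading:

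- One consequence is given for both triggers, and one of them is withdrawal of consent.
- The article's own Procedures section (Table 1) includes the t0, t1 and t2 assessments.
- The Risks and benefits section uses the word intervention elsewhere. Here it speaks of the trial procedure and, for acute suicidality, of exclusion from the study.
- The rule applies to the individual patient without regard to arm. Controls receive care-as-usual alone, so assessments are the only trial procedure left to stop for them.

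No sentence keeps t1 and t2 for stopped patients. The telephone schedule does not expressly cover them. Equally, no sentence removes them from the analysis set, so the fault is avoidable missing outcomes.

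**2. The plan's own figures.** Inputs from Sample size: d = 0.4, two-sided α = 0.05, power 0.80, about 15% loss, 240 included.

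- The two-sample t-test solution is 99.08 per arm, rounded up to 100. This matches the stated 100 per group.
- 200/(1 − 0.15) = 235.3, so 236 are needed against 240 planned.
- Analysable: 240 × 0.85 / 2 = 102 per arm.

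**3. Shift in the adjusted difference.** Let k be the net number of stopped patients (one arm minus the other) and s their t1 deficit in SD against the baseline prediction. The values of k and s are assumptions.

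Shift = k·s/102.

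| k | s (SD) | Shift (SD) | Share of d = 0.4 |
|---|---|---|---|
| 1 | 1 | 1/102 = 0.0098 | 2.5% |
| 1 | 2 | 2/102 = 0.0196 | 5% |
| 4 | 1 | 4/102 = 0.0392 | 10% |
| 2 | 2 | 4/102 = 0.0392 | 10% |

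Simulating a baseline-adjusted analysis (baseline correlation 0.5, 6,000 runs, patients kept versus lost) gives the same four shifts.

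The same relation in proportions is shift = (stop rate in the intervention arm − stop rate in the control arm) × s. With assumed rates and s from 0.5 to 1.0:

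- 5% against 2%: 0.015 to 0.03 SD.
- 5% against 0%: 0.025 to 0.05 SD.
- 10% against 0%: 0.05 to 0.10 SD.

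Equal rates and equal deficits give about zero.

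**4. Against sampling error.** The standard error of the adjusted difference is √(2(1 − r²)/102), where r is the assumed correlation between baseline and t1. It is 0.134, 0.121 and 0.100 for r = 0.3, 0.5 and 0.7. A shift of 0.039 SD is 0.039/0.121 = 0.32 of a standard error at r = 0.5.

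**5. Power.** Take d = 0.4 on the baseline-SD scale that Data analysis uses for effect sizes. The effect in residual units is then 0.4/√(1 − r²). By the noncentral t distribution:

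| Assumed r | Power at 102 per arm | Smallest n per arm with power ≥ 0.80 |
|---|---|---|
| 0.3 | 0.85 | 91 |
| 0.5 | 0.91 | 75 |
| 0.7 | 0.98 | 52 |

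Without baseline adjustment (normal approximation), power is 81.5% at 204 analysed. It falls to 79.1% with a further 5% of the 240 lost (192 analysed) and to 76.5% with a further 10% lost (180 analysed).

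**The case against.** The strongest reply is that this is a journal article. The full protocol may separate stopping the program from leaving follow-up, and the program-only reading is available. On that reading nothing is lost, and the sections on assessments, intention-to-treat and telephone contact fit together. A safety sentence may simply have no application to controls. The ambiguity is real, so loss of scores is a risk and not a certainty. But the article is not merely silent: it states a rule, with a trigger and a consequence, and the wider reading is at least as natural as the narrow one.

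Second, removing an acutely suicidal patient from the program is legitimate. Part of the suicidality text concerns exclusion before randomisation, and suicidal ideation alone leads to an algorithm rather than exclusion. Some of these t1 scores would be missing under any rule. This stands, and the fix allows for it. It does not justify ending assessment for every adverse event.

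Third, the effect may be small. The earlier efficacy trial (N = 89) reported no major adverse events, about 15% loss is already allowed for, and no difference between arms is shown. All of this stands, although the absence of major events says nothing about minor ones, which also trigger the rule. The Data Safety and Monitoring Board's review of exclusions is a safeguard for patients, but it does not restore an uncollected score.

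**Conclusion.** The concern holds and should be fixed. As written, the rule can end t1 and t2 assessment after any adverse event, and so lose primary-outcome scores for reasons tied to that outcome, against the trial's own intention-to-treat basis.

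No bias size can be claimed, because the article gives no adverse-event rates. Moving the estimate by 10% of d = 0.4 would take a net imbalance of about four stopped patients at 1 SD below prediction, or two at 2 SD. Direction depends on which arm loses more such patients. With baseline adjustment at the assumed correlations, no meaningful loss of power is expected. The case for acting is that uncollected scores cannot be recovered later, while collecting them costs almost nothing. Confidence is medium, because the program-only reading cannot be ruled out.

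**What to change.** Replace the individual stop rule with wording to this effect: an adverse event or acute suicidality may stop the intervention on clinical grounds; the patient remains in the randomised analysis set and is still asked for t1 and t2, unless consent to data collection is withdrawn or assessment is clinically inappropriate. Say that the repeated telephone contacts also apply to patients who have stopped the program.

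The cost is two or three sentences in the protocol and a slight questionnaire burden for patients who have stopped. Clinical handling of acute suicidality and the planned N = 240 do not change.

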### Dissemination

The results will be published and disseminated nationally and internationally to the scientific community as well as to the patient community and public. The main findings will be submitted for publication in a high-impact peer-reviewed journal with open-access mechanism within 12 months of study completion. Authorship eligibility will be decided based on the International Committee of Medical Journal Editors (ICMJE). We will also regularly communicate the results in lay language via press releases, social media, our own homepages and forums which are popular amongst patients. The close collaboration with PAOs in each participating country ensures adequate communication to the patient community via newsletters and yearly events, which we plan to attend in order to present the results.

### Patient involvement

The intervention has been developed based on pre-assessed needs of patients with different rare diseases [29] and was supported by the German patient organization ACHSE e.V. Within Q.RARE.LI, patients are actively involved as stakeholders when evaluating the implementability of the intervention into routine care. Moreover, the engagement of peer-counselors meets the need of a greater patient empowerment and has been formulated by the Word Health Organization as a strategy to improve care [54].

## Discussion

Q.RARE.LI aims to pave the way for widely available psychosocial support for the rare disease community. We expect to demonstrate the effectiveness of the peer-delivered psychosocial support intervention in routine care of patients with rare autoimmune liver diseases in five different national health systems. With respect to implementation outcomes, we expect high acceptability and perceived feasibility of the intervention from the perspective of patients, peer-counselors, and healthcare providers. In addition, we expect to gain a deep understanding of the implementation context in five different countries and be able to derive barriers and facilitators for implementation based on the CFIR framework. This will lead to a profound understanding of the intervention characteristics, the outer setting, the inner setting, the individuals involved as well as the process from different perspectives (including patients and healthcare providers). Identifying these contextual determinants will help us to derive appropriate implementation strategies and develop a concrete implementation plan in each country. If our hypotheses are confirmed, we will be one step closer to making targeted psychosocial support available to a large group of patients with rare diseases. Independent of the effectiveness results, the results on implementation will lead to a better understanding of the implementation conditions in five different healthcare settings and facilitate future implementation of any psychosocial support program.

With Q.RARE.LI, we pursue a transdiagnostic approach in psychosocial care. Considering the high clinical heterogeneity between different rare diseases, even among conditions of the same group such as autoimmune liver diseases, this may seem counterintuitive. However, the transdiagnostic approach offers a major advantage in psychosocial care of this patient population. At a structural level, cross-disease services are what makes comprehensive psychosocial care possible in the first place as offering disease-specific services for the multitude of different rare diseases is considered impossible [13]. At a content level, this approach is adequate as well. Despite being affected by heterogeneous clinical symptoms, patients with different rare diseases experience a variety of similar problems, including psychological burden, constraints in everyday and social life, and problems related to the healthcare system [3]. Addressing these in transdiagnostic psychological interventions can help to reach many individuals within this hard-to-reach patient population for psychosocial support.

## Data Availability

After publication of the results, de-identified individual patient data will be made publicly available through a clinical data repository. Contact person: [name], [contact].
